**Methods:**

In a randomised trial we will compare (a) Cognitive Therapy (CT) with (b) Interpersonal therapy (IPT), and (c) an 8-week waiting list condition followed by treatment of choice. One hundred eighty depressed patients (aged 18-65) will be recruited in a mental health care centre in Maastricht (the Netherlands). Eligible patients will be randomly allocated to one of the three intervention groups. The primary outcome measure of the clinical evaluation is depression severity measured by the Beck Depression Intenvory-II (BDI-II). Other outcomes include process variables such as dysfunctional beliefs, negative attributions, and interpersonal problems. All self-report outcome assessments will take place on the internet at baseline, three, seven, eight, nine, ten, eleven, twelve and twenty-four months. At 24 months a retrospective telephone interview will be administered. Furthermore, a rudimentary analysis of the cost-effectiveness will be embedded. The study has been ethically approved and registered.

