### Main research questions and Hypotheses

The following main research questions were formulated:

• Are CT and IPT effective interventions in treating the acute phase of MDD and is one therapy superior to the other?

• What are the underlying psychological mechanisms of change in CT and IPT and are these mechanisms therapy-specific?

• Are CT and IPT effective in preventing relapse or recurrence of MDD in the long-term? Is one therapy superior to the other, and if so, how can these preventive effects be explained?

In line with previous research, it is hypothesized that the amount of change in depressive symptoms after therapy will be similar in both the CT and the IPT group, indicating that both treatments are just as effective in treating depression in the acute phase [14,24,56,57]. Because both therapies originally stem from different theoretical backgrounds, we expect that both treatments target depression through different key processes. It is expected that changes in cognitive schemas, attitudes, and cognitions are the most significant contributors to symptom change in CT, whereas in IPT it is assumed that improvement of interpersonal functioning will lead to a reduction of symptoms [12,16]. With regard to the mechanisms of change, many hypotheses are possible, especially when it comes to the order of change and causal pathways that lead to recovery. Following the theories one would expect that change in cognitions (CT) and interpersonal functioning (IPT) precede symptom change. Furthermore, we expect that it is the direct comparison of explicit versus implicit measures that will elicit new insights into the underlying mechanisms of change. To the extent that implicit measures reflect uncontrollable, unaware and fast mechanisms, they can provide useful additional information as compared to explicit measures. As to the prevention of relapse, we hypothesize that both CT and IPT may reduce the risk of relapse and recurrence in the long term. However, we expect CT to prevent relapse to a greater extent, because it has shown to have an enduring effect that extends beyond the end of therapy, while IPT so far only seems to be effective in treating depression as long as the treatment is continued [58].

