### Randomisation and procedure

Eligible participants will be contacted by telephone for a baseline visit at the university. Preceding this initial visit to the research centre, participants will receive an appointment letter, including study information. This will allow them to consider their study participation well before they agree to participate (approximately one week). Furthermore, to decrease the burden of the first assessment, participants will be asked to already fill out a substantial part of the baseline questionnaires at home. Randomisation will take place after informed consent is obtained and the second part of the baseline questionnaires are filled out. In our design we prestratified groups by first (1 episode) and recurrent (> 1 episodes) depression. The researcher will press the 'assign' button on the computer screen, after which the database randomly allocates the participant to one of the treatment conditions (CT or IPT), or to the waiting list condition by using block randomisation. This waiting list condition is included because it has been frequently argued in psychotherapy research that the effect in treatment studies cannot be attributed to the intervention(s) that are studied, unless a placebo or no-treatment group is included [65]. With regard to the nature of the treatments, blinding of the participants and researchers is not possible.

In reporting the follow-up period of the CT and IPT condition in this study, we distinguish three phases; (a) the Treatment phase (baseline to 7 months); the period when therapy will be delivered; (b) The Trial follow-up phase (month 8-12) in which depression severity will be measured monthly; and (c) The Long-term follow-up phase (12 to 24 months); the period covered by retrospective assessment. All questionnaires will be administered on a computer. Pre- and post treatment assessment (baseline and 7 months) will take place at the University. All other follow-up self-report assessments will take place at home via the internet at three, eight, nine, ten, eleven, twelve and twenty-four months after inclusion.

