Productivity and Disease Questionnaire	**•**		**•**		**•**	**•**
Work and Social Adjustment Scale	**•**		**•**		**•**	**•**
Euroqol-6D	**•**		**•**		**•**	**•**
Rand 36	**•**		**•**		**•**	**•**
						
*Other measures*	**•**					
Genetic information						
Working Alliance Inventory		**•**				
Collaborative Study Psychotherapy Rating Scale	**•**	**•**	**•*****			
Working Alliance Inventory-short observer version	**•**	**•**	**•*****			

* Patients in the waiting list condition will receive the same baseline assessment, they will have a second baseline assessment at 2 months follow-up, and their 9, 14, and 26 month follow-up assessments parallel respectively the 7, 12, and 24 month assessments of the CT and IPT group. ** The following general predictors will be administered at baseline as well: demographic variables, family anamnesis, childhood experiences, life-events, reliability and expectations. *** During the treatment phase, all sessions will be videotaped. Only a random selection of tapes will be rated.

In all conditions a BDI-II will be filled out before each session during the treatment phase. After the two-year follow-up period, a modified version of the semi-structured Longitudinal Interval Follow-Up Evaluation (LIFE) [66] will be administered to retrospectively map out the course of depressive symptoms. To optimize the adherence of self-report assessments, participants will receive an email foregoing each assessment point. If one does not complete the questionnaires within one week, an email-reminder will be sent. If the participant still fails to fill out the questionnaires, a phone call will be made.

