#### Longitudinal Interval Follow-up Evaluation

The modified version of the semi-structured Longitudinal Interval Follow-up Evaluation (LIFE) [66] will be used to map out the course of depressive symptoms in the long-term follow-up phase (12-24 months). This will be administered at the end of the follow-up (24 months). We used the MDD section of the original interview, and added items on general functioning, working status, relations to others and treatment- and study experiences. The LIFE has shown to be a reliable and valid instrument for characterizing the course of several mental disorders examined retrospectively over the period of one year [84,85].

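### The reason given for not blinding researchers does not cover the month-24 telephone interviewer, so second-year relapse ratings are left open to avoidable rater bias

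*Protocol article*

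**What the plan says.** Under Randomisation and procedure the article states, giving the nature of the treatments as the reason, that "blinding of the participants and researchers is not possible". The same section has the researcher trigger allocation on screen and defines the last phase as "The Long-term follow-up phase (12 to 24 months); the period covered by retrospective assessment".

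The Methods part of the abstract adds: "At 24 months a retrospective telephone interview will be administered". The instrument is a modified, semi-structured LIFE. Its own section says that the MDD part of the parent interview was kept and that the authors "added items on general functioning, working status, relations to others and treatment- and study experiences".

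Sample size rests the 75 patients per arm on a 20-point CT-IPT difference in relapse/recurrence. Analyses assigns relapse and recurrence at 12 and 24 months to Cox regression. Under Main research questions and Hypotheses the team writes that "we expect CT to prevent relapse to a greater extent". Independent assessors appear once, under Interventions, for ratings of session videotapes.

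**The concern.** The blinding sentence is a positive statement with a reason attached, so it can be tested against that reason. Patients and therapists cannot be kept unaware of a talking therapy. Someone who telephones 17 months after the treatment phase ends (24 − 7) can be kept unaware of the allocation, at least until the patient reveals it.

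The rating at issue involves judgement. In a semi-structured interview about the past year, the rater helps to decide whether a spell reached episode threshold and when it began. Knowledge of the arm can influence both decisions. The same call also asks about treatment experiences, which invite the patient to describe the therapy. The team's stated expectation gives any such influence a possible direction. At stake is the credibility of the comparison for which the trial was sized.

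**Working it through.** **Step 1. Does the stated reason reach the interviewer?**

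| Role | Does the nature of the treatment prevent blinding? |
|---|---|
| Patient | Yes |
| Therapist (delivers only CT or only IPT) | Yes |
| Researcher who triggers allocation | Not because of the treatment, but this person may see the result |
| Month-24 LIFE interviewer | No |

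**Step 2. Which outcome data depend on the LIFE?** Table 1 shows no assessment between months 12 and 24. At month 24 the BDI-II and the DID are administered once and cannot date episodes over the preceding year. The LIFE is described as mapping that year. That it supplies the second-year events for the Cox model is therefore a strong inference, not a statement in the article.

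**Step 3. What is not exposed?**
- The BDI-II, named as the primary outcome, is self-reported.
- The assessments at months 8 to 12 are described as self-report, mostly over the internet. Table 1 calls the DID an interview, but its own section and the abbreviation list call it an inventory. I read it as a questionnaire.
- Patients who have already relapsed by month 12 have their event status fixed before the LIFE. Only those event-free at that point can have it changed by a LIFE rating. The article gives no split of expected events by year.

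**Step 4. The plan's own figure.** Inputs from Sample size: 33% relapse/recurrence at two years, a 20-point difference, two-sided α = 0.05, power 80%, 75 per arm. The second relapse rate is not stated. Taking CT 33% and IPT 53%:
- HR = ln(1 − 0.33)/ln(1 − 0.53) = 0.530.
- Schoenfeld's formula gives 79 events, and 79/(2 × 0.43) = 92 per arm.
- With 13% against 33%, Freedman's formula gives 74 per arm.

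So 75 cannot be confirmed or refuted without the missing rate. Nothing below depends on it, and masking the interviewer would not change it.

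**Step 5. Illustration by reclassified histories.** Shift in one arm's relapse rate = k/n, where k is the number of histories reclassified in one direction and n the number at risk. Both are assumptions. One basis for n is the response rate of up to 60% in Background: 0.60 × 75 = 45. That is an upper figure for response, not remission, and comes from other studies, so a lower value of 30 is also shown.

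| n at risk per arm | One history | Four histories | Four histories as share of 20 points |
|---|---|---|---|
| 75 | 1/75 = 1.3 points | 4/75 = 5.3 points | 27% |
| 45 | 1/45 = 2.2 points | 4/45 = 8.9 points | 44% |
| 30 | 1/30 = 3.3 points | 4/30 = 13.3 points | 67% |

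**Step 6. Illustration by error rate.** Suppose that true relapse risk p is equal in both arms, that a share b of CT relapses is missed, and that the same share b of IPT non-relapses is counted as relapse. The observed rates are p(1 − b) and p + (1 − p)b, so the spurious difference is b. For a two-sided 5% two-proportion test with 75 per arm and p from 33% to 53%:

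| b | Actual type I error |
|---|---|
| 2% | about 6% |
| 5% | 9% to 10% |
| 10% | 23% to 25% |

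Here b applies to the whole two-year outcome. If only second-year ratings are affected, the error rate among those ratings must be higher to produce the same b. The test is also a simplification of the planned Cox model. The table shows sensitivity and is not a forecast.

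**The case against.** The strongest reply is that the article never says who conducts the LIFE. The blinding sentence closes a paragraph about allocation, and the word researchers need not include every rater, since the tape raters are called independent assessors. Staffing of one interview is detail that an article may leave to the full protocol. This stands in part: a reader might infer that the interviewer is known to be unblinded, and the text does not establish that. It does not dispose of the point, because the article gives a general reason against blinding researchers that does not fit this role. If the full protocol does mask the interviewer, the sentence is wrong as printed.

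Other replies also stand:
- The order of questions within the LIFE is not stated. The article mentions the MDD section before the added items, so it cannot be said that the experience items come first.
- The direction of bias is possible, not certain. The team also expects similar acute effects, and both therapies are usual care at the site.
- Four histories, all in one arm and one direction, is an arbitrary choice, and 45 at risk borrows a background figure.
- Patients know their therapy. Their own recall and reporting could differ by arm even with a masked rater, so only the rater's part of the bias is avoidable.

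**Conclusion.** The point holds in a limited form. The stated reason does not justify leaving the month-24 interviewer unblinded. The rating concerned very probably determines second-year events in the endpoint that sizes CT against IPT. This rests on two inferences: that the blanket sentence covers the interviewer, since no masked assessor is described, and that the LIFE feeds the Cox analysis.

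Its size cannot be derived from the documents. On the assumptions shown, four reclassified histories are worth 5.3 points with 75 at risk and 8.9 with 45, which is between a quarter and just under half of the planned difference.

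Two stronger readings are not supported. A reader might infer that the trial's main result is compromised, but the primary outcome is self-reported and first-year relapse does not rest on the LIFE. A reader might also infer that the relapse comparison will be biased towards CT, but the documents show an opportunity and an expectation, not an effect. This is an improvement that should be made, not a flaw that invalidates the design.

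**What to change.** 1. Amend the sentence under Randomisation and procedure so that it limits the impossibility of blinding to participants and therapists, and to staff who handle allocation. State that the LIFE interviewer is masked.
2. Have the LIFE conducted by a member of the existing team without access to the allocation field and, where staffing allows, without earlier contact with that participant. The article does not show that such staff are available for every call, so the second condition is a preference.
3. Ask participants at the start of the call not to name or describe their therapy.
4. Complete and lock the MDD section before the treatment- and study-experience items are asked.
5. Record and report any unmasking.
6. State under Analyses that the LIFE provides the relapse and recurrence dates for months 12 to 24, if that is the intention.

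The cost is some scheduling, a change to database access rights and a fixed order on the interview form. Sample size, visits, instruments and treatment stay as they are. Some accidental unmasking will still occur, and participants' own recall and reporting bias will remain.

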### Interventions

The interventions will be offered at the Academic RIAGG Maastricht. At this site, CT and IPT are already delivered as treatment as usual. Interventions are written out in a treatment manual, and both treatments will contain 12 to 20 sessions of 45 minutes, depending on the individual progress of patients. Interventions will be delivered by qualified therapists, who were trained by [name] (CT) and [name] (IPT), experts in the field of depression treatment. To prevent contamination of treatment conditions, participating therapists will deliver either CT or IPT. Therapists will consult each other on current cases in biweekly consultation meetings. The CT protocol is based on the manual by Beck (1979) and is modified for the current study with a special focus on relapse prevention. IPT is based on the manual of Klerman, Weissman, Rounsaville, and Chevron (1984). CT and IPT differ in terms of target (cognitions and behaviour vs. interpersonal functioning), approach (directive vs. empathic-reflective) and method (homework assignment vs. no assignments) [27]. All sessions will be videotaped, and a random selection of tapes will be analysed by independent assessors on treatment adherence (content and quality) by using the Collaborative Study Psychotherapy Rating Scale - version 6 (CSPRS-6) [67], and on quality of therapeutic alliance using the Observer version of the Working Alliance Inventory-Short (WAI-O-S) [68-72].

### Instruments

Several instruments will be used to assess the effects of CT and IPT on depressive symptoms and other secondary outcomes. Furthermore, instruments will be used to assess the mechanisms of change and the cost-effectiveness of CT and IPT. An overview of all measurements per assessment is given in table 1.

### Clinical outcome measures

#### Beck Depression Inventory-II

The Beck Depression Inventory-II (BDI-II) [73,74] will be used as the primary outcome measure of depressive severity. The total score is the sum of the 21 items ranging from 0 to 63. Higher scores reflect more severe depressive symptoms. Several studies have shown that the BDI-II is a strong screening measure for depression [73-75].

#### Quick Inventory of Depressive Symptoms

The Quick Inventory of Depressive Symptoms (QIDS) [76] is a treatment sensitive measure of symptom severity in depression. The 16 items that measure 9 criterion domains of MDD are derived from the 30-item Inventory of Depressive Symptomatology (IDS) [77]. The QIDS has been shown to have highly acceptable psychometric properties [78].

#### Brief Symptom Inventory

The Brief Symptom Inventory (BSI) [79] is a 53-item self-report instrument that will be used to measure general psychological distress. It is derived from the SCL-90-R and several studies have demonstrated it to be an acceptable short alternative of its longer version [80,81].

#### Diagnostic Inventory for Depression

The Diagnostic Inventory for Depression (DID) will be used to assess the psychosocial impairment due to depression, and to evaluate subjective quality of life [82,83]. Psychometric analysis shows good reliability and validity [82].

#### Longitudinal Interval Follow-up Evaluation

The modified version of the semi-structured Longitudinal Interval Follow-up Evaluation (LIFE) [66] will be used to map out the course of depressive symptoms in the long-term follow-up phase (12-24 months). This will be administered at the end of the follow-up (24 months). We used the MDD section of the original interview, and added items on general functioning, working status, relations to others and treatment- and study experiences. The LIFE has shown to be a reliable and valid instrument for characterizing the course of several mental disorders examined retrospectively over the period of one year [84,85].

### Process (or mechanism) variables

#### Dysfunctional Attitudes

The Dysfunctional Attitude scale version a (DAS-A) [86-88] is a self-report scale designed to measure patterns of negative and absolute thinking in depressed patients. Respondents need to report whether or not they agree with a series of dysfunctional assumptions on a seven point Likert-Scale. With its good internal consistency and validity, it appears to be a valid measure of dysfunctional cognitions in depressed patients [89-92].

#### Attributional Style

Attributional style will be measured using the Attributional Style Questionnaire (ASQ) [93,94]. In the ASQ, participants receive 12 hypothetical events and are asked to imagine themselves in that scenario. Subsequently they have to decide what the major cause of the situation would be if it happened to themselves and rate the cause along a 7-point Likert-scale on three dimensions: Personal, Permanent and Pervasive. Depressive symptoms are associated with an attributional style in which the causes of good and bad events are attributed to internal (versus external), stable (versus unstable), and global (versus specific) causes [95]. It is hypothesized that if attributional style changes significantly during therapy, the explanations of why events happen change to external, unstable and specific. The ASQ has shown to have good psychometric properties [93].

#### Implicit measure of self-esteem

A variant of the Single Category Implicit Association Test (Sc-IAT) [96] will be administered to obtain an implicit measure of associations with the self (self-esteem). For the current study, we adapted the original Sc-IAT paradigm to specifically measure feelings of helplessness, unlovability and worthlessness, which are considered the main themes of core beliefs in depression. The test consists of 3 blocks of trials and starts with a practice block. In this block, positive and negative words are presented (all words are related to the specific core beliefs), and the task for participants is to categorize these stimuli as such by pressing the appropriate key (left or right) without making too many errors. After the practice block, there are two test blocks. In one critical block, stimuli representing the self ('me-trials') share a response key with positive stimuli, while the other key needs to be pressed for negative stimuli. In the other critical block, the target key assignment for me-trials is switched. Stimuli representing the self now share a response key with the negative stimuli. Each block is preceded by a set of instructions concerning the dimension(s) of the categorisation task and the appropriate key response. The rationale behind the Sc-IAT is that the response time will be faster when two associated concepts are mapped together on the same key, compared to when two less compatible concepts are mapped together. For example, in people with a positive sense of self-esteem, when 'valuable' and 'me' meaning words are mapped to the same key, the response time will be faster than for the non-compatible combination ('worthless' and 'me'). The Sc-IAT effect will be calculated using the improved D-Algorithm [97]. In comparison with implicit measures obtained via other measurement procedures, the Sc-IAT shows good psychometric qualities [98-101].

